## Withdrawal from the study

Patients may withdraw from the trial at any time. If a patient withdraws from the trial she will be asked if the material already collected and information about the future delivery can be collected and included in the trial data base. If the patient requests, all information about the patient will be withdrawn. This is described in the informed consent. We wish to include and follow 1000 women in our trial. In our former studies withdrawal was a very minor problem, thus we expect a similar pattern in this trial, indicating no substitute is necessary. If this

proves to be a problem in accordance to keep our desired sample size, we might open up to include additional patients as long as the inclusion period is not stopped.

## **Adherence**

Adherence will be evaluated by asking the participants about their tablet intake in a systematic manner at each visit. In addition participants will be asked to count and report their remaining tablets in connection with the telephone interview at 8 weeks postpartum. Further monitoring of the number of tablets is not required.

Good adherence is defined as consumption of  $\geq 90\%$  of the estimated drug dose during the study period. Acceptable compliance will be defined as drug consumption  $\geq 70\%$  and  $< 90\%$ .

Poor compliance is defined as  $< 70\%$  drug consumption.

## **Variables**

### *Height*

Will be measured in cm. Measured without shoes, once – at the inclusion visit

### *Weight*

Weight will be measured at each prescheduled visit, without shoes and with light clothes on.

Weight in early pregnancy and weight development through pregnancy is an important factor in almost all conditions in pregnancy.. Weight will be measured and approximated to the nearest kg.

### *Fasting plasma glucose and OGTT*

The prevalence of gestational diabetes is high among PCOS. It is important to identify impaired glucose tolerance and GDM as early as possible in pregnancy and treat it appropriately

### *The Doppler examination of the uterine artery*

Up to date ultrasound devices in daily practice will be used. Doppler ultrasound will be measured by abdominal approach. The point where the uterine artery crosses the internal iliac artery will be identified and the gate will be placed within 1 cm on each side of this point. The angle will be kept below 30 degrees. Pulsatility index (PI) will be measured on the right and left side 3 times. The lowest PI (LPI) for each side will be used in further analyses. Presence of a diastolic notch will be registered on each side.

### *Ferriman Gallwey score*

The Ferriman-Gallwey score is scored according to established standards

(<http://www.hirsutism.com/hirsutism-biology/ferriman-gallwey-score.shtml>)

To identify hirsutism in a more structured manner. See appendix.

### *Breast volume estimation*

The volume of the breasts will be estimated by specially designed cups. This will be done at inclusion and at the last visit in pregnancy. See appendix.

### **Randomization**

Randomization will be performed at the Unit for Applied Clinical Research (AKF), Department of Cancer Research and Molecular Medicine, Norwegian University of Science and Technology, Trondheim, Norway. Randomization will be in blocks of ten (5 metformin and 5 placebos) for each country. An unknown sized block will be introduced at the beginning of the inclusion in each country to make it impossible to estimate the actual study allocation of the participants.

### **Interim analyses**

No interim analyses will be performed.

### **Blinding**

The investigators at the study centers will enter patients into the web CRF at Unit for Applied Clinical Research. The participants then get a unique CRF number. The national pharmacy distributing the study medication will send the study medication to the including center. The study medication will be handed out by the investigator. When the participant is randomized, she will get a randomization number. The study drug package will have the same number as the patients randomization number.

The participants and care providers will be blinded for treatment allocation.

## **Unblinding**

In a case of emergency unblinding or breaking the codes might be necessary. The sponsor/Dr. med. [name] shall be informed as soon as possible. The code log will at all times be kept at the Hospital Pharmacy in Trondheim. Necessary unblinding can be done by the pharmacist on call at the St.Olavs Hospital.

Phone number: [name]

This information is found in the site file at each study center.

.

## **Side effects**

The most common side effects are gastrointestinal discomfort. Gastrointestinal side effects, headache and dizziness will be registered in a structured form in the CRF. Other possible and suspected side effects will be documented.

In case of suspected unacceptable side effects, the study medicine dosage will be adjusted or stopped.

All medication used by the participants will be registered.

## **Adverse events**

### *Definition*

#### *Adverse event (AE)*

An adverse event (AE) is defined as any untoward medical occurrence in a patient or clinical investigation subject administered a pharmaceutical product, which does not necessarily have a causal relationship with this treatment. An AE can therefore be any unfavourable and

unintended sign (including an abnormal laboratory finding), symptom, or disease temporarily associated with the use of a medical product, whether or not related to the medical product.

*Serious adverse events (SAE)*

Any serious adverse events (SAE) arising during the study must be reported to the principal investigator of the study within 24 hours. SAE is defined as any untoward medical occurrence that at any dose:

- Results in death,
- Is life-threatening (i.e. the patient was at risk of death at the time of the event. It does not refer to an event, which hypothetically might have caused death if it was more severe).
- Requires in-patient hospitalisation or prolongation of existing hospitalisation.

*SAE not to be reported;*

Conditions to be reported as study endpoints, **and not as SAE**, even if they are leading to hospitalization.

- Gestational diabetes
- Preeclampsia and severe hypertonia
- Preterm delivery
- Miscarriage
- Preterm rupture of membranes
- Severe intrauterine growth restriction

Protocol for The PregMet 2 Study; version 7  
2013-11-25

- Severe bleeding in pregnancy

*In the case of an SAE please refer to:* Principal investigator, Dr.med [name], St.Olavs Hospital, Trondheim,

Phone office: [contact]

Mobile phone [name]

Study [contact]

E-mail: [[contact]](mailto:[contact])

**SUSAR** (Suspected Unexpected Serious Adverse Reactions)

According to “Regulation relating to clinical trials on medicinal products for human use”, the sponsor shall ensure that all suspected adverse reactions occurring in connection with a clinical trial of drugs for human beings that are fatal or life-threatening, and which are unexpected, are reported. The same is applicable for suspected adverse reactions that are serious and unexpected

All SUSARs in Norway shall be reported individually to the Norwegian Medical Agency and to EMEA by the sponsor, Dr.med [name], within 7 days for fatal or life-threatening SUSARS and within 15 days for other serious and unexpected adverse events. The principal investigator at each site in Norway shall report all SUSARs to the sponsor within 24 hours. In the other Nordic countries the SUSARs shall be reported to the national principal investigator within 24 hours. The national principal investigator will report to the medicine agency in their country according to their regulations and to the sponsor, Dr.med [name]. SUSARs

recorded outside Norway will be reported to the Norwegian Medical Agency once a year. The following conditions will not be regarded as adverse effects, and thus they will not be reported as AE/ SAE or SUSARs:

- a) frequently occurring minor conditions in pregnancy
- Fatigue
  - Pelvic girdle pain/low back pain
  - Uncomplicated, transient dizziness
  - Uncomplicated transient headache
  - Edema
  - Vaginal yeast infection (candidiasis)
  - Varicose veins in the legs and vulva/vagina
  - Haemorrhoids
  - Uncomplicated urinary tract infection (Group-B-streptococcus in the urine, must be registered as AE)
- b) Adverse events **not to be registered** until 8 weeks post partum frequently occurring minor conditions in **post partum** until 8 weeks
- Uncomplicated, transient dizziness
  - Uncomplicated transient headache
  - Vaginal yeast infection (candidiasis)
  - Varicose veins in the legs and vulva/vagina
  - Haemorrhoids

- Minor, transient problems related to the vagina/perineum (itching, soreness, protracted minor bleeding after delivery, minor urinary incontinence)
  - Local infection, soreness, opening of episiotomy, laceration or operation scar after CS
  - Problems with breastfeeding, sore breast (these are reported elsewhere in the CRF.
- c) Offspring

All hospitalization must be reported and sustained colic (not crying a few nights)

Not reported as AE:

- Minor cold
- Problems to suckle /take breast
- Minor infections in the eyes/ umbilicus
- Stiff neck

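### The exemption of endpoint conditions from SAE reporting has no severity limit, so a fatal or life-threatening listed event judged unrelated to study drug can miss the 24-hour report

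*Protocol*

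**What the plan says.** In the Adverse events section, under Serious adverse events (SAE), the protocol states that any SAE "must be reported to the principal investigator of the study within 24 hours". It gives three alternative criteria:

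- death: "Results in death";
- danger to life, explained as "the patient was at risk of death at the time of the event";
- admission: "Requires in-patient hospitalisation or prolongation of existing hospitalisation".

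The next sub-heading, SAE not to be reported, lists conditions that are to be handled as endpoints instead of SAEs, "even if they are leading to hospitalization". The list includes "Preeclampsia and severe hypertonia" and severe bleeding in pregnancy. It also includes gestational diabetes, preterm delivery, miscarriage, preterm rupture of membranes and severe growth restriction.

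The SUSAR text that follows keeps a separate route for suspected adverse reactions that are serious and unexpected. Sites report these within 24 hours, to the sponsor in Norway and to the national principal investigator elsewhere. The Monitoring section has every SAE and SUSAR monitored, against roughly 20% of the data overall.

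**The concern.** The exemption attaches to the condition, not to one of the three SAE criteria. Its only remark on seriousness is that admission does not lift it. Nothing says whether death or danger to life does.

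A site that follows the text can therefore enter a woman who dies or nearly dies of preeclampsia, or of a severe bleed during pregnancy, as an endpoint and send no SAE report. SAE reporting is the channel that does not depend on whether the investigator suspects the drug: the protocol's own adverse event definition covers events regardless of causality. For the listed conditions that independence is lost, and the gravest cases are where it matters most. The sponsor may stop the trial under Discontinuation of the trial, but the protocol does not ensure prompt notice of these cases.

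**Working it through.** No power, alpha or sample-size figure is involved, so there is no stated figure to reproduce. The check is a comparison of texts.

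**1. Scope of the exemption.** Of the three SAE criteria, the clause mentions one (hospitalisation) and is silent on two (death, danger to life). The words "even if they are leading to hospitalization" extend the exemption to admitted cases. They do not confine it to cases whose only serious feature is admission.

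**2. Severity wording.** Three items on the list carry the word severe (hypertonia, growth restriction, bleeding). The later lists of minor conditions, under SUSAR, often limit severity with terms such as uncomplicated, transient or minor. The authors capped severity there and not here.

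**3. What the SUSAR route catches.** It needs a suspected reaction that is unexpected. The drug effects that the protocol describes are mainly gastrointestinal (Side effects, Ethics), and Ethics says no harm to mother or fetus has been reported. A fatal preeclampsia suspected to be due to study drug would thus be unexpected and still carry a 24-hour report. The listed conditions are exempted only as SAEs, whereas the minor conditions are expressly exempted from SUSAR reporting as well.

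**4. Routes side by side, for a listed condition.**

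| Case | Meets SAE definition | SAE report on the text | SUSAR route |
|---|---|---|---|
| Admission only | yes | no, expressly waived | only if suspected and unexpected |
| Fatal or life-threatening, suspected and unexpected reaction | yes | no | yes, within 24 hours |
| Fatal or life-threatening, judged unrelated | yes | no | no |

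The third row is the gap.

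**5. Monitoring.** Complete monitoring follows the SAE or SUSAR label. A case in the third row is checked only if the woman is among a site's first patients, which are monitored fully or in part, or if her visit falls in the random sample.

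**6. Context for size.** From Table 1 of the protocol, preeclampsia in PregMet 1:

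- metformin 10/135 (7.4%), placebo 5/135 (3.7%), p = 0.18, 95% CI for the difference -1.7 to 9.2 percentage points;
- both arms: (10 + 5)/(135 + 135) = 15/270 = 5.6%.

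If that rate recurred in the 1000 women planned, 1000 × 15/270 is about 56 cases. This counts preeclampsia of any severity and is not the number of missed reports. The documents give no fatal or life-threatening share, so that number cannot be derived.

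**The case against.** The best defence is that a general definition followed by a headed exception is an ordinary rule with a carve-out, not a contradiction. Because the clause names only hospitalisation, a sensible site could take it to waive only that criterion and would still report a death. That reading is available, but the text does not state it, and sites in several countries must apply the same words. Exempting endpoint conditions from SAE reporting is a legitimate choice. What remains open is its upper limit.

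Several stronger conclusions that a reader might draw are not supported:

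- **That all fatal or life-threatening listed cases escape prompt reporting.** The SUSAR route catches suspected, unexpected reactions. Preeclampsia being a known complication of PCOS pregnancy does not make it an expected reaction to metformin.
- **That severity is not recorded.** The CRF is not shown. The endpoints section lists hospitalised patients, hospital days and treatment safety, so it cannot be said that the data hold only presence or absence.
- **That the sponsor could not learn of such a case during the trial.** The Unblinding section requires the sponsor to be informed when the code is broken in an emergency. The statement "No interim analyses will be performed" and the coded groups concern comparative analysis and allocation, and do not block reporting of a single event.
- **That any haemorrhage is exempt.** Only severe bleeding in pregnancy is listed. Postpartum haemorrhage is not, and adverse events are reported until 8 weeks post partum.
- **That PregMet 1 shows a preeclampsia harm.** A split of 10 against 5 with p = 0.18 does not show one.

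**Conclusion.** The point holds in a limited form. For the listed conditions, the protocol does not keep death or danger to life reportable as an SAE. Fatal or life-threatening cases that the investigator judges unrelated can therefore miss the 24-hour report and the complete monitoring given to SAEs. This rests on reading the exemption as written, with the SUSAR route intact.

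The number affected is unknown and probably small; the 5.6% preeclampsia rate in PregMet 1 is background, not a measure of harm. The point should be corrected because each missed report would concern an event of the gravest kind and the remedy is cheap. It does not affect the primary analysis or its error rates.

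**What to change.** Add to SAE not to be reported: *The exemption waives only the hospitalisation criterion. A listed condition that results in death or is life-threatening is reported as an SAE within 24 hours, in addition to being recorded as an endpoint.*

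Such cases then also come under the complete SAE monitoring already planned, with no change to the Monitoring section. The cost is a short protocol amendment, notice to the sites and a few extra SAE forms. No visit, test or analysis changes, and routine admissions for endpoint conditions stay exempt.

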## **Discontinuation of the trial**

In case of unexpected emergencies, security problems etc the sponsor might want to discontinue the trial as a whole. If the sponsor discontinues the clinical development of an investigational product (i.e. for any or all indications, routes of administration, or dosage forms), the sponsor should maintain all sponsor-specific essential documents for at least 2 years after formal discontinuation or in conformance with the applicable regulatory requirement(s). If the sponsor discontinues the clinical development of an investigational product, the sponsor should notify all the trial investigators/institutions and all the regulatory authorities.

### **Concomitant medication**

Concomitant medication will be registered by generic name and treatment duration.

Medications taken for frequently occurring minor conditions in pregnancy (listed above) will not be registered.

The participants should not take any other vitamins, trace elements, dietary supplements or herbal medicine as long as they participate in the study. Fish oil and omega 3 can be taken

## **Management of the study**

The study will be performed according to a “penta-blind” approach.

1. The patient will be blinded for the study medication.
2. The investigator will be blinded for treatment allocation. This is the traditional “double-blind” design and represents the gold standard of pharmaceutical research; randomised double-blinded studies.
3. Obstetricians who evaluate the end points (quality check the given diagnoses) of the study will not be among those who have consulted or treated of the participants during the study. To minimize the chance to estimate the treatment allocation of the individual patient, those who evaluate end points, will only be given access to the data they need to classify the outcomes, adverse events and safety data. When this is done and the monitoring is finished the data base will be locked.
4. All statistical procedures will be performed by a statistician blinded for the actual medication; groups will be analysed only as group 1 and group 2.
5. All results presented in tables and figures, which will be part of the first major publication from the PregMet 2 Study, will be worked out before the codes are broken.

This blinding procedure will be documented at the Unit for Applied Clinical Research (AKF) in Trondheim.

6. Regional forskningsbiobank Midt-Norge is responsible for the PregMet2 study biobank. Responsible for the Regional forskningsbiobank Midt-Norge is professor [name] (leader of the Regional forskningsbiobank Midt-Norge).

### **Sub-studies of the PregMet2 study**

There are 3 sub-studies connected to the PregMet2 study

**1. The RespPreg study “Metformin in lung health in pregnant women with PCOS”**

The sub-study has a questionnaire part (run in Bergen, Trondheim and Ålesund) and a spirometri test part (run in Bergen and Trondheim).

See separate protocol, CRF and patient information/consent.

**2. The Polymeter study “Polycystic ovary syndrome metformin elimination research”**

The sub-study collects extra blood samples in pregnancy and post partum. (The substudy is run in Trondheim)

See separate protocol and patient information/consent.

**3. The CircMet study “The impact of Metformin on the fetal pulmonary and hepatic circulation” (run in Bergen)**

This study performs additional ultrasound examinations on the patients

See separate protocol, CRF and patient information/consent.

### **Statistical analyses**

Statistical analysis of the data will be performed when all data are collected and quality checked. Data will be analyzed by an experienced statistician at Unit for Applied Clinical Research according to the “pentablind” approach.

The main outcome (late abortions and preterm births) will be the end points by intention to treat (ITT) analyses. However, secondary “per protocol” analysis will also be performed. The metformin group will be compared to the placebo group using non-paired parametric and non-paired non-parametric methods as appropriate. Only two-sided tests will be used.

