### *Preterm birth*

The WHO defines preterm labour as labour occurring before 37 weeks of pregnancy or before 259 days of pregnancy (A). As prognosis depends on gestational age at birth, we further subdivide preterm deliveries into following groups (23):

- Late preterm birth                      34 - 36+6 weeks
- Moderately preterm birth            32 - 33+6 weeks
- Very preterm birth                      28 - 32+6 weeks
- Extremely preterm birth              < 28 weeks

About 10% of preterm deliveries are extremely preterm, another 10 % very preterm and approximately 80 % moderately or late preterm deliveries.

The obstetric precursors leading to preterm birth are:

1. Delivery for maternal or fetal indications, in which labor is either induced or the infant is delivered by prelabor caesarean section;
2. Spontaneous preterm labor with intact membranes; and
3. Preterm premature rupture of the membranes (PPROM), irrespective of whether delivery is vaginal or by caesarean section (24).

Figure 1 (25, 26).

[figure not shown]

Preterm delivery is a major contributor to neonatal morbidity and mortality (27).

Epidemiological risk factors such as socioeconomic status and ethnicity seems to be important (26). Infections, uterine distension and anomaly are other known factors related to

preterm birth. However, the causes of preterm delivery are still essentially unknown and seem to be multifactorial (25).

Former preterm delivery is a significant risk factor. However, almost 50 % of preterm births occur without any identified cause or risk factor (25). The incidence of preterm birth is rising in most western countries, Norway included (28). This occurs despite all attempts to treat and prevent preterm birth.

The fact that former preterm labour is a strong risk factor, indicate a genetic or otherwise individual disposition. And the more or less universal rise in preterm birth rates in the Western world indicates that environmental or lifestyle risk factor changes are involved

Incidence of preterm labour:

Incidence in Norway (B) : 1980: 5.6 %

1995: 7.5 %

1999: 7.9 %

Incidence in the USA (C): 1980: 8 %

1995: 12 %

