### *Study medication*

- Metformin 500 mg x 2 daily the first week and then 1000 mg x 2 daily from the second week to delivery.

Protocol for The PregMet 2 Study; version 7  
2013-11-25

- Placebo 1 tablet x 2 daily the first week. And then 2 tablets x 2 daily from the second week to delivery.
- To counteract a possible metformin action on folic acid and vitamin B12 levels, patients will be advised to take the daily dose of folic acid recommended in the country of the study centre. Further, one daily multivitamin tablet containing vitamin B6 and B12 will be recommended.
- Both metformin and placebo are produced by Weifa A/S. The tablets will be packed into boxes at the Hospital Pharmacy in Trondheim. After randomization the medication will be sent to cooperating pharmacies at the study site.
- The Hospital Pharmacy in Trondheim is responsible for medical accounting in the trial.
- A separate drugaccountability log will be registered at each site.

*Patients included in the PregMet 2 Study*

- The overall intention and philosophy of the trial, is that included patients should receive the recommended and appropriate treatment available at each country and centre.
- Participation in the study does not limit any kind of diagnostic evaluation, examination or treatment option regarded as necessary during pregnancy.
- The participants in the PregMet 2 study can however not participate in other medical trials during the actual pregnancy.

- Patients can only be included in the PregMet 2 Study once.

*Progesterone treatment to prevent preterm delivery*

In Iceland vaginal progesterone administration is used to prevent preterm delivery according to national guidelines;

1. In multiparous women who had former preterm delivery and
2. In women where cervix is found to be < 15 mm before gestational week 32. There are however no screening program for cervix length for asymptomatic women.

These treatment regimens interfere with the primary endpoint of the PregMet study. Therefore to avoid protocol violation and ethical conflict we decide the following:

1. At study centres in countries where progesterone is used prophylactic in multiparous women with former preterm birth, only nulliparous women will be included in the study.
2. In women with signs or symptoms of imminent preterm delivery, the routine treatment at the study centre should be given, - included vaginal progesterone treatment.

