3. Vaginal progesterone treatment in such cases of imminent preterm delivery will be registered as a secondary endpoint.

If the progesterone treatment routine is introduced in other participating countries during the on-going study, these countries will adhere to the instructions above.

*Pre-inclusion evaluation - screening*

- Information (verbal and written to the potential participating woman).
- Signed written informed consent.
- Confirming the diagnosis of PCOS; anamnestically and from patient records

□

Vaginal ultrasound examination to verify intrauterine viable singleton fetus (visualised heart beats), gestational age  $< 12+6$  weeks. (CRL  $< 65$  mm or BPD  $< 23$  mm)

- Blood tests:
- fasting plasma or serum glucose,
- serum ALAT
- serum creatinine

Standardized interviewer-administered CRF will be used to obtain self-reported data on former medical and gynecologic/obstetric history, ethnicity, and employment, smoking habits, study medication and concomitant medication. Biometric variables, including height (measured only at inclusion), weight, blood pressure, and heart rate, are recorded at inclusion and at each pre-scheduled visits at gestational week 19, 28, 32 and 36.

*1st pre-scheduled visit:*

Inclusion gestational age  $\leq 12^{+6}$  weeks

- Written general diet and lifestyle information recommended to pregnant women from the national health authorities in each country will be given.
- Anamnestic data
- Physical examination
- Blood pressure

Protocol for The PregMet 2 Study; version 7  
2013-11-25

□

- Weight and height  
Breast-size estimation
- Hirsutism score (<http://www.hirsutism.com/hirsutism-biology/ferriman-gallweyscore.shtml>)
- Vaginal ultrasound examination:
- Visualized heart activity
- CRL and /or BPD measured
- Description of the ovaries
- Fasting blood samples (both serum and full blood) for freezing
- 2 hour OGTT (Fasting and 2h serum glucose to be measured locally)
- Questionnaire on depression EPDS (standard questionnaire used in and after pregnancy in routine pregnancy follow-up)

*2nd pre-scheduled visit:*

Gestational age 19 ± 1 week

- Anamnestic data
- Physical examination
- Blood pressure
- Weight
- Ultrasound examination:
- Mid-pregnancy determination of term

□

Doppler measurement of the uterine artery (OPTIONAL)

- Fasting blood sample (both serum and full blood) for freezing
- Fasting blood sample for glucose

*3rd pre-scheduled visit:*

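### Allocation is blocked by country, but the stated arm comparison uses neither country nor previous preterm birth: valid, slightly inefficient, and free to improve

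*Protocol*

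**What the plan says.** On allocation, the Protocol's Randomization section states: "Randomization will be in blocks of ten (5 metformin and 5 placebos) for each country". Country is therefore a stratification factor. Parity and previous preterm birth are not.

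On enrolment, the progesterone paragraphs under Study medication say "In Iceland vaginal progesterone administration is used to prevent preterm delivery according to national guidelines". At centres in a country that gives it prophylactically after an earlier preterm birth, "only nulliparous women will be included in the study". Iceland is the only country named. The rule can spread: "If the progesterone treatment routine is introduced in other participating countries during the on-going study, these countries will adhere to the instructions above".

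On prognosis, the Preterm birth part of the Introduction says "Former preterm delivery is a significant risk factor" and, a little later, that "former preterm labour is a strong risk factor". Obstetric history is collected on the CRF (Pre-inclusion evaluation - screening).

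On analysis, the primary endpoint is a yes/no outcome for each woman, late miscarriage or preterm birth (The endpoints of the study). Statistical analyses sets an intention-to-treat primary analysis with two-sided tests, and describes the method only as: "The metformin group will be compared to the placebo group using non-paired parametric and non-paired non-parametric methods as appropriate". Country, parity and previous preterm birth do not appear in the analysis or power sections.

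**The concern.** When allocation is balanced within a factor that predicts the outcome, the difference between arms varies less from trial to trial than an unstratified standard error assumes. A test that ignores the factor is then a little conservative and gives up some power. Here the factor is country. Event rates may differ between countries for ordinary reasons, and in at least one country the enrolment rule also changes the mix of women.

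Previous preterm birth is a separate matter. It is not a stratum, so blocking does not balance it, and a chance imbalance stays in an unadjusted estimate. The protocol itself calls it strong, and the data are already collected.

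At stake is a small amount of precision in a trial that expects about 75 primary events (500 × 0.10 + 500 × 0.05) and adds no allowance for withdrawal. The validity of the result is not at stake.

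**Working it through.** **1. The plan's own figure.** Inputs from Power calculation: 10% against 5%, two-sided alpha 0.05, power 85%. With pooled variance and no continuity correction,

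n = [1.960·√(2·0.075·0.925) + 1.036·√(0.10·0.90 + 0.05·0.95)]² / 0.05² = [0.730 + 0.384]² / 0.0025 ≈ 497 per arm.

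The protocol states 500, where power is 85.2%. Its 80% table (280, 430, 720) comes back as 283, 435, 721. The sample size was therefore computed as for an unstratified comparison of two proportions.

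**2. Stratifying by country.** Assumed, because the protocol gives none of it: three equal countries, control rates pᵢ averaging 10%, and metformin halving the rate in each country (xᵢ = pᵢ/2). With arms balanced within country and no effect, the ratio of the true to the assumed variance is

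r = mean[pᵢ(1−pᵢ)] / [0.10·0.90], and the plain test's true level is 2[1 − Φ(1.960/√r)].

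For 5/10/15%: r = [(0.0475 + 0.0900 + 0.1275)/3]/0.09 = 0.9815; 1.960/√0.9815 = 1.978; level 0.0479.

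Power = Φ[(0.05 − 1.960·SE₀)/SE₁], where
- SE₁ = √(mean[pᵢ(1−pᵢ) + xᵢ(1−xᵢ)]/500);
- SE₀ for the plain test = √(2·0.075·0.925/500) = 0.01666;
- SE₀ for the stratified test = √(mean[2mᵢ(1−mᵢ)]/500), with mᵢ = (pᵢ + xᵢ)/2.

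| Control rates | r | True level, plain | Power, plain | Power, stratified | Gain (points) |
|---|---|---|---|---|---|
| 8/10/12% | 0.9970 | 0.0497 | 85.26% | 85.31% | 0.05 |
| 5/10/15% | 0.9815 | 0.0479 | 85.41% | 85.72% | 0.31 |
| 3/10/17% | 0.9637 | 0.0459 | 85.59% | 86.19% | 0.60 |

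**3. Adding previous preterm birth.** Simulation of 10,000 trials per setting, N = 1000, arms balanced within four countries of 600, 200, 150 and 50 women. All of the following is assumed: the smallest country is nulliparous-only; 40% of women elsewhere are parous; country odds ratios are 1, 1.3, 0.8 and 1; parous women without a previous preterm birth have odds ratio 0.7 against nulliparous women. The marginal rates are set to 10% and 5%. CMH is the Cochran-Mantel-Haenszel test.

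| Odds ratio, previous preterm birth | Share of parous women | Power, plain | CMH by country | CMH by country and history | Gain, last against plain |
|---|---|---|---|---|---|
| 3 | 10% | 85.41% | 85.46% | 85.57% | 0.16 |
| 5 | 10% | 86.44% | 86.47% | 87.14% | 0.70 |
| 5 | 25% | 85.25% | 85.35% | 86.56% | 1.31 |

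Under no effect, every test rejected in 0.050 to 0.054 of trials (Monte Carlo standard error √(0.05·0.95/10,000) = 0.002).

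**4. Chance imbalance.** Assume 5% of 1000 women, that is 50, have a previous preterm birth, with 25–30% risk against 10% overall. The difference in their number between arms has standard deviation about √50 = 7.1, so a two-SD imbalance is about 14 women. That shifts the event difference by 14 × 0.15 to 14 × 0.20, or 2 to 3 events, against an expected difference of 25.

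**The case against.** The strongest reply is that strata and covariates commonly belong in a statistical analysis plan, which is not at hand. The method sentence leaves the choice open, names no test and does not exclude a stratified or adjusted analysis. A reader might infer that the protocol commits to a plain two-sample test; it does not. Nor is the wording wrong for a binary endpoint: chi-square-type tests can be classed as non-parametric, and the same sentence must also serve measured outcomes such as birth weight. All of this stands. What remains is that the protocol fixes country as a blocking factor, then describes the comparison without it and sizes the trial as unstratified.

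Other stronger readings also fail:
- **Bias or inflated type I error from the nulliparous-only rule.** Allocation is 1:1 within each country, so a different parity mix cannot confound the arms, and the unstratified test errs slightly on the conservative side.
- **Omission of the strongest risk factor.** The protocol says significant and strong, without ranking, and it says this of former preterm delivery, not of parity.
- **Several nulliparous-only countries.** Only Iceland is named; others follow only if they adopt the routine.
- **A saving of 20 to 50 women per 1000.** That range comes from adding the outcome variance explained by country (1.2% for assumed rates 6/10/14%) to that explained by previous preterm birth (0.8–3.9% for assumed prevalence 3–8% and risk 25–30%). A primary analysis stratified by country alone recovers only the first part, 1.2% of 1000 or about 12 women.

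**Conclusion.** The point holds as a free improvement of minor severity. The protocol blocks by country and describes an arm comparison without strata or covariates. An unstratified test would be valid. If country rates differ, its standard error is slightly too wide: the true level is about 0.046 to 0.050, and the loss about 0 to 0.6 power points against a country-stratified test. The gain reaches about 1.3 points only when previous preterm birth is also used, and only under the most favourable setting tried (odds ratio 5, a quarter of parous women affected). The sample size does not change.

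These sizes rest on assumed country sizes, country rates, parity mix and odds ratios, none of which the protocol gives. The direction does not depend on them: accounting for a factor already balanced by design cannot be expected to cost anything material, provided the strata are not too small.

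**What to change.** In Statistical analyses, state the primary intention-to-treat analysis as a Mantel-Haenszel risk difference, with the risk ratio alongside, stratified by country and tested two-sided at 5%. Say that very small countries are merged into one stratum, and fix that rule before the codes are broken.

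Add one pre-specified supportive analysis: a logistic model with treatment, country and previous preterm birth in three classes (nulliparous, parous without, parous with). Its odds ratio is on a different scale from the primary risk difference and serves as a check on chance imbalance, not as a replacement.

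The cost is wording only: no new data, no change in sample size or conduct. If a separate analysis plan already says this, the protocol need only refer to it.
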